## Abstract

**Background:**

*Marma* therapy, a traditional Ayurvedic practice, involves the precise stimulation of *marmas* (vital points that regulate *prana* [vital energy]) and alleviates musculoskeletal pain and dysfunction. While historical texts describe *marma*’s role in pain relief, no randomized controlled trials have evaluated its efficacy and safety in lumbar disc herniation (LDH)–related radiculopathy.

**Objective:**

This study aims to explore the efficacy and safety of *marma* therapy in a commonly occurring painful condition, namely, radiculopathy due to LDH.

**Methods:**

Selected patients with LDH and radiculopathy are randomized into 2 groups using a computer-generated random number sequence. The participants in group 1 (the trial arm) are treated with *marma* therapy for 4 weeks, and those in group 2 (the control arm) receive physiotherapy for 4 weeks. All the participants in both groups are given an oral medicine, *trayodashanga guggulu*, an Ayurvedic formulation, for 12 weeks.

**Results:**

As of November 2025, a total of 90 patients have been enrolled in both groups. Data analysis is ongoing. The study will be reported following standard guidelines for reporting randomized controlled trials. Clinical trial results will be disseminated through conferences and publication in a peer-reviewed scientific journal.

**Conclusions:**

*Marma* therapy, if proven effective and safe in pain management, can improve the quality of life of patients with LDH. This protocol can be useful in designing large-scale studies to establish this noninvasive and safe treatment as an alternative modality for the management of neurological pain, such as radiculopathy.

## Introduction

Low-back pain (LBP) with radiculopathy due to lumbar disc herniation (LDH) is a leading cause of disability worldwide, affecting approximately 5% to 10% of patients with chronic LBP [1,2], with up to a 70% lifetime prevalence [3]. Radiculopathy, characterized by radiating pain, sensory deficits, and motor weakness along the affected nerve root, significantly impairs the quality of life (QoL) and functional capacity [4]. Conventional treatments, including analgesics, physical therapy, epidural steroid injections, and surgery, often provide incomplete relief and carry risks of adverse effects, recurrence, and high costs [5].

Given these challenges, complementary and alternative medicine approaches, including Ayurveda, are increasingly explored for neuropathic pain management. Existing research on Ayurvedic therapies for LBP and radicular pain suggests potential benefits. However, the evidence is preliminary and primarily based on case reports. Only a few randomized controlled trials (RCTs) on Ayurvedic procedures for LBP have been published. One of them shows promising results for *Abhyanga* (Ayurvedic oil massage) in chronic LBP [6]. *Marma* therapy, an Ayurvedic intervention, involves stimulating vital energy points (*marma* points) to restore physiological balance and alleviate pain. While *marma* therapy is traditionally used in Ayurveda for musculoskeletal dysfunctions [7], its efficacy in LDH-associated radiculopathy remains understudied in rigorous clinical trials. Studies on yoga and acupuncture, both of which share conceptual similarities with *marma* therapy in terms of energy modulation, have demonstrated efficacy in LBP [8]. However, no RCT has specifically evaluated *marma* therapy for LDH-associated radiculopathy.

This study aims to assess the efficacy of *marma* therapy in pain management and functional improvement in patients with LDH-associated radiculopathy, compared with standard physiotherapy. The findings will contribute to evidence-based integrative approaches for neuropathic pain management. This is the first RCT that evaluates the efficacy and safety of *marma* therapy in LDH-associated radiculopathy compared to standard physiotherapy. The primary objective of this study is to evaluate the efficacy of *marma* therapy in reducing pain associated with lumbar radiculopathy caused by intervertebral disc herniation. Outcomes include pain intensity, measured by the Visual Analog Scale (VAS); functional disability, assessed by the Oswestry Disability Index (ODI); and QoL, evaluated by the 36-item short form health survey (SF-36). This study also assesses the safety of *marma* therapy among the selected patients. The study aims to fill a critical evidence gap in integrative pain management.

## Methods

### Participants, Interventions, and Outcomes

#### Study Design

This is a randomized, open-label, parallel-arm, active-controlled clinical trial.

#### Study Setting

The study is conducted at the outpatient department (OPD) of the Main Campus Hospital, Uttarakhand Ayurved University, Dehradun, Uttarakhand, India.

### Eligibility Criteria

#### Inclusion Criteria

Participants of any sex, aged 30-60 years, diagnosed with lumbar radiculopathy with unilateral radiating pain (either left or right lower limb) due to intervertebral disc herniation confirmed by magnetic resonance imaging (MRI; disc herniation between L3 and S1 levels at a single or double level) and without any evident neurological deficit are included. Participants having a positive straight leg raise test (SLRT; ipsilateral or contralateral pain in the leg, buttock, or back at ≤70° of leg elevation, with pain typically worsened by dorsiflexion of the ankle or neck flexion after slowly lowering the leg until the patient no longer feels pain) and those who are willing to adhere to the study protocol for a period of 3 months are included in this study.

#### Exclusion Criteria

Patients who are indicated for surgical intervention for disc herniation (eg, those with severe motor deficit [motor power of the lower limbs assessed through the Medical Research Council Manual Muscle Testing scale ≤3] or severe spinal stenosis); those with excruciating pain that cannot be managed by conservative treatment; or those with evident foraminal stenosis, conjoint nerve root, or perineural cyst are excluded. Patients who have received nonpharmacological interventions, such as physiotherapy, traction, or manual therapy, for the management of LDH in the last 3 months are also excluded. Patients having a history or evidence of osteoporotic lumbar fracture, spinal trauma, spinal malignancy, or inflammatory or infective diseases that affect spinal morphology (such as ankylosing spondylitis, spondylodiscitis or inflammatory spondylitis, spondylolisthesis, Pott disease, piriformis syndrome, or sacroiliitis); a history of spinal surgery in the last 2 years; or epidural fibrosis are excluded. Patients with cauda equina syndrome or neurological deficits, such as foot drop, limb muscle wasting, or bowel or bladder incontinence or nonambulatory patients with monoplegia, paraplegia, or hemiplegia are also excluded. The presence of other medical conditions presenting numbness and pain in the lower extremities (such as diabetic polyneuropathy, peripheral vascular disease, motor neuron disease, multiple sclerosis, or stroke), cognitive impairment, or major coexisting medical conditions such as cancer, chronic obstructive pulmonary disease, cardiovascular disease, or severe hepatic or renal dysfunction is also an exclusion criterion. Patients with obesity (BMI ≥30 kg/m^2^), those not suitable for MRI (eg, those with metallic implants such as pacemakers or hearing aid implants), or those having any other condition that limits the participation of the patient, as determined by the investigator, are also excluded from the study.

### Interventions

The participants were randomly allocated to 1 of 2 groups. Both groups receive a different nonpharmacological therapy along with a common Ayurvedic formulation for oral consumption. Group 1 received *marma* therapy for 4 weeks and *trayodashanga guggulu* for 12 weeks, and group 2 received physiotherapy for 4 weeks along with *trayodashanga guggulu* for 12 weeks.

*Marma* therapy is a procedure that includes stimulation of *kshipra* (point located between the great toe and the second digit of the lower limb)*, gulpha* (point located posterior to the medial malleolus)*, indrabasti* (point located 8 fingerbreadths above the first skin fold of the ankle joint)*, katikataruna* (points located bilaterally along the vertebral column over the hip bone), and *janu* (point located posterior to the knee joint) *marma* of the affected limb thrice daily. Out of 108 *marma* points mentioned in the Ayurvedic texts, these were selected for the said condition, based on the clinical experience of the principal investigator.

*Trayodashanga guggulu* is a classical multiherb Ayurvedic formulation mentioned in the Ayurvedic Formulary of India, Part-1 [9]. This medicine is procured from a Good Manufacturing Practice–certified pharmacy, and its quality is in compliance with the standards mentioned in the Ayurvedic Pharmacopoeia of India [10].

### Delivery of Interventions

The mode of delivery, frequency, and duration of each intervention are described below.

For *marma* therapy, the participants in the trial arm are advised to wear loose and comfortable clothing (without ties, belts, stockings, or such binding clothes) and lie down in the prone or supine position, as per the site to be stimulated. Each of the 5 *marma* points is stimulated in an upward-to-downward direction in each session. *Marma* points are stimulated by gentle pressure or vibration using the pulp of the thumb or fingers and the inner side of the knuckle. Each session includes 18 to 20 stimulations to each of the said *marma* points (1 stimulation lasts for 0.8 seconds). Three such sessions are done each day for 4 weeks. *Marma* stimulation in female patients is typically performed first in the left extremity, followed by the right extremity, and vice versa in male patients.

For physiotherapy—educational training (eg, advice to avoid sitting for long periods, forward bending, lifting heavy object from ground using leg with knee bending, and trying to tighten the stomach muscles) along with electrotherapy (transcutaneous electrical nerve stimulation with frequency of 20 Hz; pulse width of 100 µs; continuous mode; and 2 channels for 15 minutes, with electrodes placed along the lines of the T12 and S1 vertebrae and intensity increased slowly to a tolerably painful level); hot pack therapy (water at a temperature of 54 °C placed at the lower back for at least 15 minutes, with the patient in hook-lying position); therapeutic exercises suggested based on the case (mostly including drawing-in maneuver, multifidus activation and training, cat-camel exercise, arm lifts and bracing, leg lifts and bracing, single knee-to-chest exercise, and exercises to promote mobility, strength, and range of motion in the lower back); and manual therapy (flexibility training) were provided for 30 minutes per session, 5 sessions per week, for 4 weeks. The participants in the control arm are instructed on the therapeutic exercises and provided with a chart outlining the final positions and necessary instructions.

*Trayodashanga guggulu* tablets, weighing 500 mg each, are given as oral medication to the study participants in both groups at a dose of 1 g thrice daily, 2 hours after meals, with lukewarm water for 3 months. Participants are allowed to take oral analgesics as rescue medication for pain relief upon telephonic consultation with the investigator. Ongoing medications reported at baseline for any chronic condition (not mentioned in the exclusion criteria) are also continued by the study participants as concomitant medication. Participants who are unwilling to continue, are noncompliant with the study procedure, or meet any exclusion criteria during the study period are withdrawn from the study.

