### Data Analysis

After verification for accuracy, all collected data will be anonymized prior to statistical analysis. All analyses will follow both the intention-to-treat and per-protocol principles to evaluate the robustness and sensitivity of the results. Any missing or incomplete responses will be addressed through Bayesian imputation. To make the imputation robust, regression-based imputation will also be applied if sufficient information is available in the data. Furthermore, the data will be used for descriptive analysis. Categorical variables will be described as frequencies and percentages, while continuous variables will be summarized as mean (SD) or median (IQR), depending on the distribution of the data (normal or skewed). Inferential analyses will be performed after descriptive analysis of the data. For within-group comparisons, data will be analyzed using the paired 2-tailed t test or the Wilcoxon signed-rank test, depending on the distribution of the data for pre-post observations. Between-group comparisons will be performed using the independent-samples *t* test or Mann-Whitney *U* test, depending on the normality of the data.

Repeated-measures ANOVA or the Friedman test will be used for within-group and between-group analyses of the outcomes assessed at multiple time points. The generalized estimating equation and the repeated-measures ANOVA, along with factor analysis, will also be performed if any confounding factors are found during the analysis. Analysis of covariance will be performed if baseline differences between groups are observed. A 2-sided significance level of 5% will be considered for all analyses. All statistical analyses will be performed using Stata software (version 16.1; StataCorp).

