## Results

Participant recruitment was initiated on April 4, 2022, and as of November 2025, a total of 90 patients have been enrolled. Of these, 70 (77.8%) study participants have completed the final follow-up. Data cleaning is now complete, and the results will be published once the analysis is complete. The final report and data interpretation are expected to be submitted for publication in 2026.

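### Withdrawing noncompliant or worsening participants from the study, not only from therapy, undermines the stated intention-to-treat analysis

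*Protocol article*

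**What the plan says.** All places are in the protocol article.

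- **Delivery of Interventions.** Besides those unwilling to go on, participants who "are noncompliant with the study procedure, or meet any exclusion criteria during the study period are withdrawn from the study".
- **Exclusion Criteria.** The list that this rule carries into the study period includes "Patients who are indicated for surgical intervention for disc herniation", "those with excruciating pain that cannot be managed by conservative treatment" and "Patients with cauda equina syndrome or neurological deficits, such as foot drop, limb muscle wasting, or bowel or bladder incontinence".
- **Outcome Measures.** The primary outcome is the change from baseline in 10 cm VAS pain at day 30 and at 3 months.
- **Participant Timeline, Table 1.** Pain is assessed at baseline and repeatedly from day 7 to day 90. No visit or assessment is described for someone already withdrawn.
- **Data Analysis.** "All analyses will follow both the intention-to-treat and per-protocol principles to evaluate the robustness and sensitivity of the results". On missing data: "Any missing or incomplete responses will be addressed through Bayesian imputation", with regression-based imputation as well if the data allow it.
- **Results.** On the 90 enrolled: "Of these, 70 (77.8%) study participants have completed the final follow-up". Neither the reasons nor the arm is given for the others.

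**The concern.** Eligibility criteria are written to decide who enters a trial. Here they also decide who remains in it. A participant who develops a surgical indication, uncontrollable pain or a neurological deficit after randomisation has had a poor outcome, and the pain criterion measures the same thing as the primary endpoint. Under the rule that participant leaves the study, possibly before day 30 or day 90 can show the deterioration. Missing data are then linked to the outcome itself.

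The noncompliance limb causes a second problem. Intention-to-treat is meant to keep participants who did not adhere, and per-protocol to leave them out. If nonadherent participants are withdrawn from the study, the observed data behind the intention-to-treat analysis move towards the per-protocol set. Agreement between the two analyses, which the article offers as a check of robustness, then says less than it appears to.

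At stake is the between-arm VAS comparison. If withdrawal for worsening is more common in one arm, that arm looks better than it was.

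**Working it through.** **Step 1. The article's own figures.** Completers: 70/90 = 77.8%, as stated. Not reported as completers: 90 − 70 = 20, and 20/90 = 22.2%. Planned attrition (Sample Size) was 20%, and 72/0.80 = 90 reproduces the enrolment target. Observed non-completion is therefore close to plan, and the number lost is not in itself the problem.

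**Step 2. Can imputation repair it?** Values recorded before withdrawal can inform the imputation, and anyone withdrawn after day 30 already has the day-30 value. Two gaps remain:

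- If deterioration occurs between visits and triggers withdrawal, the last recorded VAS precedes it.
- If the rule is applied as written and assessment stops at withdrawal, nobody who met a worsening criterion is observed afterwards. The data then hold no later course from which an imputation model could learn.

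Imputation from observed data would therefore tend to give such participants values resembling those of people who stayed.

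**Step 3. Possible size (illustration).** Inputs: 45 per arm and a 1-point design difference (Sample Size); 20 non-completers (Results). Assumptions, not in the article: n1 and n2 of the 20 fall in the two arms, and their true VAS is on average d cm worse than imputed, with the same d in both arms.

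True arm mean = imputed arm mean + d × n/45, so

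shift in the arm difference = d × (n1 − n2)/45.

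| Split of the 20 | d = 1 | d = 2 | d = 3 |
|---|---|---|---|
| 10/10 | 0 | 0 | 0 |
| 12/8 | 0.09 | 0.18 | 0.27 |
| 15/5 | 0.22 | 0.44 | 0.67 |

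For example, 2 × (12 − 8)/45 = 0.18 and 2 × (15 − 5)/45 = 0.44. Against the 1-point design difference these are 18% and 44%. The shift favours the arm that lost more participants.

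The zero in the first row needs equal gaps as well as equal numbers. With gaps d1 and d2 the shift is (d1 × n1 − d2 × n2)/45. A 10/10 split with gaps of 3 and 1 gives (30 − 10)/45 = 0.44.

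**The case against.** The case on the other side has force on several points.

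- **A reader might infer that intention-to-treat is impossible.** It is not. The article plans imputation and records pain from day 7, so all 90 can be analysed as randomised. What stands is that the result rests on imputing data whose absence may depend on the outcome.
- **A reader might infer that withdrawn participants lose all their outcomes.** Nothing says that earlier values are discarded. The article describes no later assessment but does not expressly forbid it, and the full protocol, which is not shown, may settle this.
- **A reader might argue that the rule removes the whole control arm**, because the exclusions include "Patients who have received nonpharmacological interventions, such as physiotherapy, traction, or manual therapy, for the management of LDH in the last 3 months". That is strained. The time window naturally refers to the period before screening, and taken literally the criterion would catch marma therapy too, since the article calls both treatments nonpharmacological. Seventy participants completed, so the rule was not applied in this way.
- **A reader might expect more withdrawals under marma because it is given three times a day.** By the article's own figures, a session is 18 to 20 stimulations × 0.8 s × 5 points = 72 to 80 s, so three sessions take 216 to 240 s, about 4 minutes of stimulation a day. Physiotherapy sessions last 30 minutes, and participants in both arms are called daily. This supports neither the direction nor the size of an imbalance.
- **The 20 non-completers may not have been withdrawn under this rule.** Loss to follow-up or withdrawn consent would produce the same count. A 2 cm gap is also large: 2/1.36 = 1.5 times the SD used in Sample Size, for a group that may include the merely unwilling.
- **Analysis detail may sit in a statistical analysis plan that is not shown.** That is fair for the choice of primary analysis set and for sensitivity analyses. It does not reach the withdrawal rule, which the article states and which pulls against its own analysis principle.

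**Conclusion.** The point stands in limited form. As worded, the rule removes participants from the study for reasons that arise after randomisation, and some of those reasons are failure on the primary outcome. No later assessment is described. This weakens the announced intention-to-treat analysis without making it impossible, and it blunts the comparison with per-protocol.

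The size of any bias is unknown. It depends on how many of the 20 left because of worsening, in which arm, and how far their true VAS lay from the imputed value. None of these is reported. On the assumptions shown, the shift runs from nothing to 0.67 of the 1-point design difference. The upper end needs both a 15/5 split and a 3 cm gap, and no row of the table should be read as an estimate. The documents do not show that differential withdrawal occurred.

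**What to change.** **Wording.** Reconcile Delivery of Interventions with Data Analysis by separating two events: stopping therapy, and leaving follow-up. Participants who stop or do not comply with therapy, or who develop an exclusion condition, stay in scheduled outcome assessment unless they withdraw consent. Decisions to stop therapy remain with the clinicians and are not altered by this change. State also whether outcomes were in fact collected after therapy stopped. With enrolment and data cleaning complete, the new wording does little for data collection here, but the article offers its protocol as a basis for larger studies, where it would matter.

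**Analysis, still feasible because results are not yet reported.**

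1. Keep all 90 in the intention-to-treat set as randomised, and name that analysis as primary.
2. Use every VAS value collected at scheduled visits, including any recorded after therapy stopped. Scores recalled long afterwards cannot replace day-30 or day-90 values.
3. Tabulate the 20 non-completers by arm, reason and last visit, identifying those withdrawn for noncompliance and those withdrawn for worsening.
4. Add a sensitivity analysis that treats withdrawal for worsening as an unfavourable outcome, for example by imputing those participants d cm worse over a range of d. Specify and date it before the arms are compared; if the comparison has already been seen, say so.

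**Cost.** Revised wording, one table and one extra analysis. The estimated effect may turn out less favourable.

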### Outcome Measures

The primary outcome of this study is a reduction in pain intensity in the lumbosacral region and legs (radiating pain) perceived by participants, assessed as the change in the 10 cm VAS score at day 30 and after 3 months from baseline.

The secondary outcomes of this study are improvement in functional disability due to LDH, assessed by the ODI, version 2.0; change in neurodynamic evaluation, assessed using the SLRT; improvement in QoL, assessed by the SF-36; comparison of dependence on allopathic analgesics; and assessment of safety and acceptability of the *marma* therapy in patients with LDH, assessed by the incidence of adverse events (AEs) associated with the therapy and compliance of patients to *marma* therapy.

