### Sample Size

A previous study that included physiotherapy as an intervention reported a mean VAS score for back pain of 3.05 (SD 1.36) points after treatment [11]. This was considered to anticipate an improvement of at least 2.79 points after *marma* therapy. Assuming a between-group difference of 1 point, with 80% power at 5% level of significance, the derived sample size was 72 participants. Furthermore, assuming a 20% attrition rate, the final sample size for this study was 90 participants, randomly allocated to the 2 groups in a 1:1 ratio (n=45, 50% participants per group). The effect size will be determined after the data analysis is completed.

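### The primary VAS outcome is read at day 30 and at 3 months, each at an unadjusted 5%, with no rule saying which result decides the trial

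*Protocol article*

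**What the plan says.** Under Outcome Measures, the protocol article names one primary outcome, a "reduction in pain intensity in the lumbosacral region and legs (radiating pain) perceived by participants", which is "assessed as the change in the 10 cm VAS score at day 30 and after 3 months from baseline". Two time points are joined by one conjunction, with no ranking and no success criterion.

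Under Data Analysis it sets the error level for everything at once: "A 2-sided significance level of 5% will be considered for all analyses". No split of alpha, order of testing or other adjustment is given.

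The same section says: "All analyses will follow both the intention-to-treat and per-protocol principles to evaluate the robustness and sensitivity of the results". Neither population is named as the primary one.

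Several between-group methods are listed. One sentence reads: "Between-group comparisons will be performed using the independent-samples *t* test or Mann-Whitney *U* test, depending on the normality of the data". Another reads: "Repeated-measures ANOVA or the Friedman test will be used for within-group and between-group analyses of the outcomes assessed at multiple time points". Generalized estimating equations and analysis of covariance follow, each under a condition. None of these is identified as the test that decides the primary outcome.

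The Sample Size section works from a single 1-point between-group difference at 80% power and 5% significance. It takes its SD from a study that "reported a mean VAS score for back pain of 3.05 (SD 1.36) points after treatment".

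**The concern.** Two time points at 5% each, with no rule for combining them, leave open what a positive trial means. The two readings answer different questions. The randomised therapies last 4 weeks, so day 30 is close to the end of treatment. The 3-month reading comes about two months later, when both arms are taking only the shared oral medicine. A split result, significant at one time and not at the other, is quite possible, and the article does not say how it would be judged.

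This is more than a detail left for an analysis plan. The article does address the significance level, and what it fixes is 5% for every analysis. Read as written, each primary time point is tested at the full 5%.

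Timing matters too. The Results section reports that 90 patients are enrolled and data cleaning is complete, and the abstract describes analysis as ongoing. A rule written down before the between-group results are seen is credible; one chosen afterwards is not.

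**Working it through.** **Inputs from the article.** Primary time points: 2 (Outcome Measures). Level: 0.05 two-sided for each analysis (Data Analysis). Difference 1 point, SD 1.36, power 80%, 72 participants before attrition and 90 after, 1:1 allocation (Sample Size). The correlation r between the two test statistics is not given, so it is an assumption, shown over a range.

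**The plan's own figure.** Per arm, n = 2 × SD² × (z for alpha + z for power)² / difference².
- At two-sided 0.05: 2 × 1.36² × (1.960 + 0.842)² = 29.03, so 30 per arm and 60 in total. The t-based version gives 31 per arm, 62 in total. The stated 72 is not reproduced.
- The attrition step is reproduced: 72 / (1 − 0.20) = 90.
- At two-sided 0.025: 2 × 1.36² × (2.241 + 0.842)² = 35.16, so 36 per arm and 72 in total. This equals the stated number. Other unstated routes also reach 72, for example 60 × 1.2, so the match is not evidence that a split was intended.

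**Reading A: success at either time point.** Under the null at both, the false-positive rate is 1 − P(|Z1| ≤ 1.96 and |Z2| ≤ 1.96), with Z1 and Z2 bivariate normal with correlation r.

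| Assumed r | Chance of at least one false positive |
|---|---|
| 0 (independent) | 1 − 0.95² = 9.75% |
| 0.3 | 9.5% |
| 0.5 | 9.1% |
| 0.7 | 8.3% |
| 0.9 | 7.0% |

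Counting only false claims in favour of marma therapy, the range for r = 0.9 to 0.3 is about 3.5% to 4.8%, against a nominal 2.5%.

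**Reading B: success at both time points.** The false-positive rate cannot exceed 5%, because each test alone is limited to 5%. The cost is power. With 36 per arm, the expected z is 1 / (1.36 × √(2/36)) = 3.12. Power per time point is Φ(3.12 − 1.96) = Φ(1.16) = 87.7%. Joint power, taking a 1-point effect and SD 1.36 at both times, is 78.4% at r = 0.3, 79.7% at r = 0.5 and 81.5% at r = 0.7.

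**Reading C: one repeated-measures test decides.** There is one test at 5% and no inflation.

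**After a fix.** A fixed sequence keeps the overall error at 5% and leaves the first time point its full power. A split at 0.025 each gives 81.0% power per time point with 36 per arm, and 79.8% with 35 per arm (the 70 completers reported so far, if evenly divided).

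**The case against.** The strongest reply is that inflation arises only under Reading A, which the article nowhere states. The time points are joined by a conjunction that can be read as requiring both, and a between-group repeated-measures analysis is planned that could serve as a single overall test. This stands: the 7.0% to 9.5% is conditional. It does not remove the point, because the article does not choose among the readings and ranks none of its listed tests.

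A second reply is that a condensed article may leave the testing order to a plan not shown, and that the personnel assessing the primary outcome are described as unaware of allocation. Such a plan may exist. But the article itself fixes 5% for all analyses and names two primary time points, and blinded assessment does not settle which one decides.

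Three stronger readings are tempting, and the article does not support them.
- **Back and leg pain as two further tests.** Two sites are named, but the text refers to one VAS score and Table 1 has one pain assessment row. Separate site ratings or tests are not established, so no error figure should be attached to them.
- **Per-protocol as a second chance to succeed.** The stated purpose of running both populations is robustness and sensitivity. The fair criticism is only that neither is named primary.
- **A serious loss of power if both time points must succeed.** On the stated SD, joint power is close to the planned 80%.

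**Conclusion.** The point holds as a missing decision rule. The article sets two primary time points, applies an unadjusted two-sided 5% to each, and names neither a decisive test nor a primary population. Should either time point be allowed to carry the claim, the type I error is about 7.0% to 9.5% instead of 5%. That range rests on approximately normal test statistics and on assumed correlations of 0.9 to 0.3. Should both be required, or one repeated-measures test decide, the error stays within 5%. Joint power under the both-required rule is then about 78% to 81% (r = 0.3 to 0.7), assuming 36 per arm and the same 1-point difference and SD of 1.36 at both times.

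A reader might infer that the trial's false-positive rate is already known to be inflated, or that the deciding result will be picked after the fact. The article shows neither; it shows only that nothing in it rules these out.

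**What to change.** Before the between-group comparisons are run, record in a dated amendment, through the route described under Protocol Amendments:

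1. One decisive between-group test, in the intention-to-treat population, at one named time point, at two-sided 5%. Day 30 is one natural choice because it marks the end of the randomised therapy, but the choice belongs to the sponsor.
2. The other time point is tested at 5% only if the first is significant.
3. Per-protocol results are supportive.
4. The VAS is one combined rating of back and leg pain, if that is the case; if not, which rating is primary.

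Requiring both time points, or splitting alpha at 0.025 each, would also control the error. Because the abstract already calls analysis ongoing, the amendment should state whether anyone had seen between-group results when it was written.

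The cost is a few sentences and no new data. The small downside of the fixed sequence is that the second time point cannot be claimed as confirmed if the first fails.
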